### Data collection

Participants will receive three automated notifications to complete follow-up measures at 6 and 12 months, one being the initial invitation to ask them to complete the online questionnaires and reminders at 1 week and 2 weeks later if they are not complete. Participants will receive a £10 gift voucher via email when they complete the 6 month follow-up questionnaires online. If, after 6 weeks, participants have not completed the 6 month follow-up questionnaires online, paper-based questionnaires will be sent with a £10 gift voucher for high-street stores (regardless of paper-based questionnaire completion). If paper-based questionnaires are not returned after 2 weeks of being sent, research staff (blind to group allocation) will phone participants to request limited responses over the phone (the EORTC); a maximum of two phone contacts per participant will be made. The procedure will be the same for 12 month follow-ups but with no further vouchers given. If at any stage the participant indicates that they would not be willing to complete any further measures, no further contact will be made regarding the follow-ups. At study completion, the usual care (wait list) group will be given access to the Renewed website. Participants will be asked if they would like a copy of the study results, and if so whether they would prefer to receive these by email or post.

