### Secondary research questions

Does the Renewed intervention, with or without human support, result in a difference in QoL at 12 month follow-up compared with treatment as usual?Is the Renewed intervention, with or without human support, more cost-effective than usual care in improving QoL in cancer survivors?Does the Renewed intervention, with or without human support, result in a difference in psychological and overall well-being (including low mood and fear of cancer recurrence) at 6 month and 12 month follow-up?Does the Renewed intervention, with or without human support, help to reduce the risk of secondary cancers (recurrence, metastatic cancer or another form of cancer)?

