### Randomisation and blinding

After online screening, patients will complete online consent and baseline measures. LifeGuide software will then randomise each participant to one of the three study groups using computer-generated random numbers. Once randomised, participants will be informed of their allocation and, if in one of the intervention arms, given access to Renewed. Randomisation will be stratified by cancer type: breast/prostate/colon and by EORTC score (high/low QoL; 64 or less/65–85 taking 65 as the lower 25% CI from previous study data^36^). Blinding of randomisation is ensured by the use of automated computer software. Blinding of patients to the intervention is not possible. Participants will be informed online as to which group they have been allocated to immediately and will also be sent notification via email. Practice staff involved in the support arm of the trial will be notified by email when one of their patients is randomised to the Renewed + Support arm of the trial so that they can provide support.

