**Process measures**			
TAQ		x	
PEI			x
Website satisfaction and usage			x
PETS			x
Usage of other interventions during past year			x

Demographics include gender, age, marital status, years of education, ethnicity, height and weight and are taken at baseline;

EQ-5D-5L, Euro-Qol; EORTC QLQ-c30, European Organization for Research and Treatment of Cancer Quality of Life Questionnaire-c30 as primary outcome; FRRS, Fear of Relapse/Recurrence Scale; HADS, Hospital Anxiety and Depression Scale; MYCAW, Measure Yourself Concerns and Well-being; PA, Physical activity checker; PEI, Patient Enablement Instrument; Website satisfaction measure; PETS, Problematic Experiences of Therapy Scale; TAQ, Treatment Appraisal Questionnaire.

The primary outcome of QoL will be measured using the total score on the EORTC QLQ-c30.^35^ The EORTC has 30 items and contains five functioning subscales: physical, emotional, social, role and cognitive and eight symptom subscales: pain, fatigue, nausea and vomiting, dyspnea, sleep problems, loss of appetite, constipation and diarrhoea, financial impact and overall quality of life. Each item has a four-point response scale from ‘not at all’ to ‘very much’ and scores are calculated using a linear conversion to create a score from 0 to 100. It is one of the most widely used measures for health-related QoL in cancer research.^52^

The Fear of Relapse/Recurrence Scale^53^ has been modified to three items so that ‘I will probably have a relapse in the next 5 years’ and ‘I am certain that I have been cured of cancer’ are omitted as they do not apply to those on Active Surveillance. The Patient Enablement Instrument (PEI) was modified so that it asks about confidence and understanding relating to health as a result of using the website as opposed to receiving support from a doctor (PEI^54 55^). Data regarding website and/or app usage (eg, pages accessed, time spent on each page) will be downloaded using LifeGuide software. A medical record notes review will be conducted after 12 month follow-up to extract NHS and Personal Social Service use. This will enable collection of data pertaining to clinical status including cancer recurrence. Online questions will be used to collect patients’ personal costs. The EQ-5D-5L^56 57^ which measures medical QoL (QALY) will be collected at baseline, 6 months and 12 months. We will apply the UK tariff to translate the EQ-5D-5L to utility scores.

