#### Health economics

Published unit costs (Personal Social Services Research Unit, British National Formulary and national reference costs) will be applied to itemised resource usage in calculating total cost per person. The health economic analysis will include cost effectiveness (£/unit of primary outcome) and cost utility (£/EQ-5D-5L QALY) analysis. The costs of the study will be from an NHS perspective with exploration of a quasi-social perspective including the time required by patients interacting with the intervention. The study will identify and quantify the resources required to deliver the intervention, and any impact on NHS service usage and personal costs. We will explore the potential change in NHS service use and change in the pattern of use of such services, such as whether the new intervention will reduce medication (eg, depression related drugs), GP consultations and community nurse and special service usage. The key resource usage of the intervention covers nursing support time, software. Personal costs will be collected on time off work (both patients/carers), cost of use of internet (personal time) and costs of over-the-counter medications. The economic analyses of both costs, QoL (EORTC and QALY), provided minimally worthwhile improvements are shown, will be summarised in terms of incremental cost effectiveness ratios and cost effectiveness acceptability curves.

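### The last-resort telephone contact takes only the EORTC, so participants reached only by phone have no EQ-5D-5L at that visit and the cost-utility analysis must impute it

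*Protocol article*

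**What the plan says.** The Data collection section sets out an escalating follow-up. An online invitation is followed by two reminders, and a paper questionnaire is posted to those who have not responded after six weeks. "If paper-based questionnaires are not returned after 2 weeks of being sent", research staff blind to allocation "will phone participants to request limited responses over the phone (the EORTC". At most two calls are made per participant. For the later visit, "The procedure will be the same for 12 month follow-ups but with no further vouchers given".

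Table 2 and the text under Measures schedule the EQ-5D-5L at all three time points: it "will be collected at baseline, 6 months and 12 months", and the UK tariff converts it to utilities. The Health economics section plans two analyses: "cost effectiveness (£/unit of primary outcome") and "cost utility (£/EQ-5D-5L QALY) analysis". The matching secondary research question asks whether Renewed is "more cost-effective than usual care in improving QoL in cancer survivors".

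Three further statements bear on the point:

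- Randomisation and blinding: "After online screening, patients will complete online consent and baseline measures", and randomisation follows.
- Statistical analysis: missing data are handled by chained-equations multiple imputation, with complete cases as a sensitivity analysis.
- Measures: NHS and Personal Social Service use is taken from a medical notes review after the 12-month follow-up.

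**The concern.** The call is the last attempt to obtain data from people who have not responded by any other route. As scripted, it recovers one outcome and leaves out the only source of utilities. The gap is also structural: no phone-only participant has an EQ-5D-5L at the visit in question. Any relation between EORTC score and utility used to impute their values must be borrowed from online and paper responders, and nothing observed in the phone group can check it.

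Two outcomes meant to inform the same economic question would then be observed in different samples. Phone-only participants would contribute an observed EORTC at that visit but no observed utility. In the complete-case sensitivity analysis they would count for the EORTC at that visit and drop out of the QALY analysis.

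Keeping the call short has a clear rationale at 6 months, when it rescues the primary outcome. The rationale is weaker at 12 months, where the EORTC is itself a secondary outcome and the QALY belongs to another secondary question.

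**Working it through.** **1. The plan's own figure.** The article gives no figure for phone-only response or for EQ-5D-5L completeness. The figure it does give is the sample size for the EORTC at 6 months, and it reproduces:

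- A standardised difference of 0.3, 80% power and alpha 0.05 (two-sided, assumed) give 175.4 per group, so 176.
- 176 × 3 = 528 per cancer type, and 528 × 3 = 1584.
- 1584 / 0.80 = 1980.
- The design effect is 1 + (8 − 1) × 0.03 = 1.21, and 1980 × 1.21 = 2395.8, so 2396. The recruitment aim is 2500.

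This rests on the EORTC alone, which the call does collect, so the point does not touch it.

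**2. What is observed for someone reached only by phone at a visit.**

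| Quantity | Source in the article | Available? |
|---|---|---|
| Baseline EQ-5D-5L | Completed online before randomisation | Should be |
| EORTC at that visit | Telephone call | Yes |
| EQ-5D-5L at that visit | Online or paper questionnaire only | No |
| EQ-5D-5L at the other follow-up | Depends on response at that visit | Possibly |
| NHS and Personal Social Service use | Notes review | Independent of questionnaire response |

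**3. Effect on the individual QALY.** The article does not state how QALYs are computed. Assume linear interpolation between visits, with utilities u0, u6 and u12 and time in years:

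QALY = 0.5 × (u0 + u6)/2 + 0.5 × (u6 + u12)/2 = 0.25 u0 + 0.50 u6 + 0.25 u12.

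On that assumption a missing 6-month utility leaves half of the weight to be imputed, and a missing 12-month utility leaves a quarter.

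**4. How many people.** The number without a utility at a visit is 2500 × p, where p is the share of randomised participants reached only by phone. The article does not give p. Each 1% is 2500 × 0.01 = 25 participants. Over an assumed range, purely to show scale:

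| Assumed p | Participants with EORTC but no EQ-5D-5L at that visit |
|---|---|
| 2% | 50 |
| 5% | 125 |
| 10% | 250 |
| 20% | 500 |

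**5. Precision.** Suppose that the 20% loss describes the EORTC after the telephone step, which is also an assumption. EQ-5D-5L completeness at a visit is then 0.80 − p. The complete-case standard error rises by √(0.80/0.75) = 1.03 at p = 5% and √(0.80/0.70) = 1.07 at p = 10%. The loss of precision is modest. The more important issue is that the missing values all fall among late responders.

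**The case against.** The strongest reply is that the plan chose this openly. After an online invitation, two reminders and a posted questionnaire, it keeps the final contact for the primary outcome. Nothing in the article promises the EQ-5D-5L by phone, and Table 2 lists measures and times, not modes of collection. This stands: the plan neither contradicts itself nor contains an error here.

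The second reply is that missing data are already provided for. Multiple imputation is planned for any missing data, baseline utilities should be in hand, and the phoned EORTC can serve as a predictor from the same visit. Phone-only participants are therefore better placed for imputation than complete non-responders. This also stands, and it reduces the concern. It does not remove it, because imputed utilities remain a weaker substitute for answers that could have been obtained on the call.

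A reader might infer several stronger things that the article does not support:

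- *That the call causes the missing QALYs.* The participant's non-response online and on paper causes them. The call recovers an EORTC score that would otherwise be lost too.
- *That these people have no EQ-5D-5L at all.* The gap is confined to the visit completed by phone.
- *That the cost-effectiveness question as a whole is compromised.* The cost-per-EORTC analysis keeps its outcome data, and NHS-perspective service use comes from the notes review. Only the QALY side of the cost-utility analysis is affected.
- *That the affected share doubles over two visits.* That requires that nobody is reached only by phone at both. The article gives no overlap, and late responders may well be late twice.

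**Conclusion.** The point holds as a cheap improvement to a secondary economic outcome. At each follow-up, participants reached only by phone have no EQ-5D-5L for that visit, and their QALY rests on imputation that the same call could have made unnecessary where the participant was willing to answer. The primary analysis and the sample size are untouched.

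The size is unknown. The only arithmetic that the article supports is 25 participants per visit for each 1% of 2500 reached only by phone. The wider table and the standard-error ratios are illustrations under assumed shares. They are also upper limits on what the change could recover, since some people would decline the extra questions and some would lack the other follow-up utility anyway. The conclusion assumes that the call is carried out as described, with the EORTC alone.

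**What to change.** In Data collection, change the content of the telephone contact at both 6 and 12 months to the EORTC first, then the EQ-5D-5L. Keeping the EORTC first protects the primary outcome if the participant ends the call early.

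This is a script change. It needs no extra staff and no extra contacts, because the calls are already being made and the limit of two per participant stays. The downside is a slightly longer call, with some risk that a reluctant participant stops before the second instrument. In that case the position is the same as under the present plan.

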#### Sub-study examining follow-up questionnaire design

There has been extensive research into how the design and presentation of questionnaires affects response rates and response quality (see^51^ for an overview). Two versions of the 12 month outcome measures will be used, to test whether completion rates can be increased by enhanced presentation. Users will be randomised to either the control (‘normal’) outcome measures or the enhanced outcome measures. For both versions, the wording and scales will remain the same, but the presentation (eg, use of images, page layout and messages encouraging completion) will be altered for the enhanced version.

### Measures

Table 2 presents a list of the measures and when they will be presented to participants. Measures will be collected via the website.

**Table 2 T2:** Measures and times presented

Measure	Baseline	Six months	**12** Months
**Primary outcome**			
EORTC QLQ-c30	x	x	x
**Secondary outcomes**			
HADS	x		x
FRRS	x		x
EQ-5D-5L	x	x	x
PA	x		
MYCAW	x		x
Personal costs data for heath economics			x
**Process measures**			
TAQ		x	
PEI			x
Website satisfaction and usage			x
PETS			x
Usage of other interventions during past year			x

Demographics include gender, age, marital status, years of education, ethnicity, height and weight and are taken at baseline;

EQ-5D-5L, Euro-Qol; EORTC QLQ-c30, European Organization for Research and Treatment of Cancer Quality of Life Questionnaire-c30 as primary outcome; FRRS, Fear of Relapse/Recurrence Scale; HADS, Hospital Anxiety and Depression Scale; MYCAW, Measure Yourself Concerns and Well-being; PA, Physical activity checker; PEI, Patient Enablement Instrument; Website satisfaction measure; PETS, Problematic Experiences of Therapy Scale; TAQ, Treatment Appraisal Questionnaire.

The primary outcome of QoL will be measured using the total score on the EORTC QLQ-c30.^35^ The EORTC has 30 items and contains five functioning subscales: physical, emotional, social, role and cognitive and eight symptom subscales: pain, fatigue, nausea and vomiting, dyspnea, sleep problems, loss of appetite, constipation and diarrhoea, financial impact and overall quality of life. Each item has a four-point response scale from ‘not at all’ to ‘very much’ and scores are calculated using a linear conversion to create a score from 0 to 100. It is one of the most widely used measures for health-related QoL in cancer research.^52^

The Fear of Relapse/Recurrence Scale^53^ has been modified to three items so that ‘I will probably have a relapse in the next 5 years’ and ‘I am certain that I have been cured of cancer’ are omitted as they do not apply to those on Active Surveillance. The Patient Enablement Instrument (PEI) was modified so that it asks about confidence and understanding relating to health as a result of using the website as opposed to receiving support from a doctor (PEI^54 55^). Data regarding website and/or app usage (eg, pages accessed, time spent on each page) will be downloaded using LifeGuide software. A medical record notes review will be conducted after 12 month follow-up to extract NHS and Personal Social Service use. This will enable collection of data pertaining to clinical status including cancer recurrence. Online questions will be used to collect patients’ personal costs. The EQ-5D-5L^56 57^ which measures medical QoL (QALY) will be collected at baseline, 6 months and 12 months. We will apply the UK tariff to translate the EQ-5D-5L to utility scores.

### Statistical analysis

SPSS, Stata and Excel software will be used to evaluate outcomes. All participant data will be analysed, including those who have withdrawn, unless participant/s specifically request that their data be removed from the data set. All participants will be analysed on an intention to treat basis, that is, as randomised with any missing data imputed using a chained equations multiple imputation model. Complete cases analysis will be undertaken as a sensitivity analysis.

Linear regression models will be used for the analysis of continuous variables, controlling for baseline values, stratification variables, practice as a cluster variable, and also controlling for potential confounding variables as appropriate, both for the overall trial sample and for each clinical subgroup (breast, prostate, colon). Results will be produced for the trial overall and within each cancer type. We will undertake pre-specified subgroup analyses, including exploring possible mediators and moderators in the context of the process analysis. These analyses will be set out in full in the Statistical Analysis Plan prior to the final follow-ups.

To examine how the design and presentation of questionnaires affects response rates and response quality, we will compare the initial completion rate for the control outcome measures versus the enhanced outcome measures using a factorial design where participants will be allocated to see the normal or enhanced questionnaires. A ratio of 1:2 (normal:enhanced) will be used when allocating participants to get a feel for how the enhanced questionnaire presentation might impact on study completion, given that unenhanced questions are already presented at baseline and 6 months.

#### Health economics

Published unit costs (Personal Social Services Research Unit, British National Formulary and national reference costs) will be applied to itemised resource usage in calculating total cost per person. The health economic analysis will include cost effectiveness (£/unit of primary outcome) and cost utility (£/EQ-5D-5L QALY) analysis. The costs of the study will be from an NHS perspective with exploration of a quasi-social perspective including the time required by patients interacting with the intervention. The study will identify and quantify the resources required to deliver the intervention, and any impact on NHS service usage and personal costs. We will explore the potential change in NHS service use and change in the pattern of use of such services, such as whether the new intervention will reduce medication (eg, depression related drugs), GP consultations and community nurse and special service usage. The key resource usage of the intervention covers nursing support time, software. Personal costs will be collected on time off work (both patients/carers), cost of use of internet (personal time) and costs of over-the-counter medications. The economic analyses of both costs, QoL (EORTC and QALY), provided minimally worthwhile improvements are shown, will be summarised in terms of incremental cost effectiveness ratios and cost effectiveness acceptability curves.

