## Aims and hypotheses

The aim of the Renewed trial is to evaluate the effectiveness and cost-effectiveness of two trial arms using an intervention designed to improve QoL in breast, colon and prostate cancer survivors: the first arm will be given access to a digital intervention (Renewed) and the second will be given access to Renewed accompanied by brief human support.

The research aims to answer the following questions:

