### Sample size and power calculation

The primary outcome is QoL as measured by the total EORTC score at 6 months. The study is powered to detect a standardised effect size of 0.3, consistent with our previous internet-based behavioural interventions.^37^ The key pairwise comparison is each of the two intervention groups versus controls. To detect a difference of 0.3 standard mean difference in any pairwise comparison between intervention and control for 80% power and alpha=0.05 requires 176 intervention participants in each intervention group and 176 controls, giving a total of 528 participants per cancer type. In order to explore the difference in the key subgroups (breast, colon and prostate cancers), this requires that we include 528 participants in each of the three clinical groups. This gives a total of 1584 participants, or 1980 allowing for 20% loss to follow-up. Even though this is an individually randomised design cluster effects are possible: if we assume eight patients per intervention group per practice then to allow for clustering at a practice level and assuming an intraclass correlation coefficient (ICC) of 0.03 then the inflation factor is 1.21 (1+ (8–1*0.03)), which will require 2396 participants. Allowing for some leeway in our assumptions, we will aim to recruit approximately 835 patients per cancer type (total n=2500).

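### The cost-effectiveness ratios and acceptability curves are conditional on a worthwhile improvement being shown, although the aim and the secondary question on cost-effectiveness are unconditional

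*Protocol article*

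**What the plan says.** Four places in the protocol article bear on this.

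- **Aims and hypotheses.** The trial is to "evaluate the effectiveness and cost-effectiveness of two trial arms using an intervention designed to improve QoL". Effectiveness and cost-effectiveness are joint aims.
- **Secondary research questions.** One question reads "Is the Renewed intervention, with or without human support, more cost-effective than usual care in improving QoL in cancer survivors". It does not depend on the answer to the primary question.
- **Health economics, opening.** "The health economic analysis will include cost effectiveness (£/unit of primary outcome) and cost utility (£/EQ-5D-5L QALY) analysis". This is also unconditional. Later the section adds "We will explore the potential change in NHS service use and change in the pattern of use of such services", including "whether the new intervention will reduce medication (eg, depression related drugs), GP consultations".
- **Health economics, last sentence.** The analyses of costs and of QoL (EORTC and QALY), "provided minimally worthwhile improvements are shown, will be summarised in terms of incremental cost effectiveness ratios and cost effectiveness acceptability curves".

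Only the last of these makes an output depend on the results. The article does not say how large an improvement must be, on which outcome, at which time point or in which arm.

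**The concern.** Cost-effectiveness is a statement about two differences taken together, in cost and in effect, with their joint uncertainty. An arm with a small or uncertain gain in quality of life may still be good value if it costs little or saves resources. It may equally be poor value with a clear gain if it costs too much. A rule that looks first at whether an improvement has been shown, and only then decides whether to present the joint result, leaves out part of what the question asks.

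The acceptability curve gives the probability that an option is cost-effective at each willingness-to-pay value. It exists to describe decisions under uncertainty, so withholding it because the effect is uncertain defeats its purpose.

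Two things are at stake. A named secondary question could lack the summary that answers it, in a trial that plans to look for changes in NHS use. And the ratios that are published would come only from results that had already passed a favourable test.

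**Working it through.** **1. The text.** The aim, the secondary question and the statement that the cost-effectiveness and cost-utility analyses will be included are unconditional. The proviso applies to the form in which results are summarised: the ratios and the curves. Costs and effects reported separately do not say how likely an arm is to be cost-effective at a given value per QALY. That needs the joint summary, which is what the proviso can remove.

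**2. The plan's own sample size.** Inputs from Sample size and power calculation: "The study is powered to detect a standardised effect size of 0.3" and "80% power and alpha=0.05 requires 176 intervention participants in each intervention group and 176 controls".

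- n per group = 2(1.960 + 0.842)² / 0.3² = 174.4, so 175. The stated 176 gives 80.4% power, so it reproduces (two-sided).
- 176 × 3 groups × 3 cancer types = 1584.
- 1584 / 0.8 = 1980 for 20% loss.
- Design effect 1 + (8 − 1) × 0.03 = 1.21, and 1980 × 1.21 = 2395.8, so 2396.

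The effective number analysed over the whole trial is therefore 1584, or 528 per arm. With the target of 2500 it is 2500 × 0.8 / 1.21 / 3 = 551.

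**3. How often the summary would be withheld.** Standard error of a difference between arms, in SD units: √(2/528) = 0.0615. For a true effect d:

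- gate at p<0.05 in favour of Renewed: P(withheld) = 1 − Φ(d/SE − 1.96)
- gate at an observed difference of at least t: P(withheld) = 1 − Φ((d − t)/SE)

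For example, at d = 0.1 with the p<0.05 gate: 0.1/0.0615 = 1.625, 1.625 − 1.96 = −0.335, and 1 − Φ(−0.335) = 0.63.

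| True effect (SD) | p<0.05 | Observed ≥0.1 | Observed ≥0.2 | Observed ≥0.3 |
|---|---|---|---|---|
| 0 | 97.5% | 94.8% | 99.9% | about 100% |
| 0.10 | 63% | 50% | 95% | 99.9% |
| 0.15 | 32% | 21% | 79% | 99% |
| 0.20 | 10% | 5% | 50% | 95% |
| 0.30 | 0.2% | 0.1% | 5% | 50% |

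With 551 per arm, the p<0.05 figures at 0.1 and 0.2 SD become 62% and 9%. All the gates are assumptions; the article supports none of them over the others.

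**4. Selection.** Under the p<0.05 gate, the mean estimate among trials that pass is d + SE × φ(a)/(1 − Φ(a)), with a = 1.96 − d/SE. At d = 0.1: a = 0.335, and 0.1 + 0.0615 × 0.377/0.369 = 0.163 SD. This applies to the outcome on which the gate is set.

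**5. Why the curve is informative without a shown effect.** Invented inputs, to show the mechanism only: QALY gain 0.005 (SE 0.01), cost SE £100, no correlation, £20,000 per QALY. The SE of net benefit is √((20,000 × 0.01)² + 100²) = £224.

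- Cost difference −£100: net benefit 20,000 × 0.005 + 100 = £200, and Φ(200/224) = 0.81.
- Cost difference +£100: net benefit £0, and the probability is 0.50.

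The QALY effect is the same and far from established (0.005/0.01 = 0.5 standard errors), yet the economic conclusion differs because the costs differ.

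**The case against.** - **The analyses are promised anyway.** The section says without condition that cost-effectiveness and cost-utility analyses will be included and that resource use will be quantified. This stands. A reader might infer that the whole economic evaluation is gated and that the secondary question would go unanswered; the text does not support that. A cost saving would still be visible. What may be lost is the joint summary.
- **A ratio is unstable when the effect difference is near zero.** True, and probably the reason for the clause. It argues for net monetary benefit and for stating dominance. It gives no reason to withhold an acceptability curve, which has no such instability.
- **The improvements meant could include cost improvements.** The sentence does not say which count. If a worthwhile saving also qualified, the case of a saving with little QoL gain would pass the gate. The more natural reading is an improvement in outcome, but the ambiguity is real, and it is a further reason to reword.
- **The threshold may be defined elsewhere.** A condensed article may leave the value to a fuller plan, so its absence is not treated as a fault. The condition itself is stated here, and no value would remove it.
- **The figures depend on assumed gates.** Accepted. The section mentions no p-value. The 0.3 SD effect is justified by earlier internet interventions, not as a minimum worthwhile difference.

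**Conclusion.** The point holds, with a limited reach. The article states a results-dependent rule for presenting the ratios and acceptability curves, and that rule does not fit its own unconditional aim and secondary question. It affects the summary of a secondary analysis. The primary analysis, the sample size and the data collected are untouched.

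No single figure for its size is supported. At true effects of 0.1 to 0.2 SD, the chance of withholding runs from about 5% to over 99% across the gates considered. The 63% and 10% illustration assumes a p<0.05 gate, 528 effective participants per arm and a normal approximation.

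Two stronger inferences should be resisted. The trial's effect estimates would not be biased in general: the EORTC result is analysed and reported whatever it shows, and selection touches only the published ratios, and those directly only if they use the gated outcome. Nor does the plan predict NHS savings; it says that it will explore a possible change in service use.

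**What to change.** Delete the proviso from the last sentence of Health economics. State instead that, for each Renewed arm against usual care and whatever the effectiveness result, the report will give:

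- incremental costs, incremental QALYs and incremental EORTC score, with confidence intervals;
- incremental net monetary benefit and the acceptability curve;
- the incremental cost-effectiveness ratio where it can be interpreted, with dominance stated otherwise.

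The cost is one clause of text and modest extra analysis. The cost and EQ-5D-5L data are already being collected, and sample size and participant burden do not change.
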